#### Outcomes at 1 month

2.5.4

Patients will be contacted by telephone at 1 month to ask the following questions:

(1)Are you experiencing any persisting pain at the site of surgery? If yes, please provide details.(2)What is your average daily pain score, on a scale of 0 to 10 (NRS)?(3)Are you continuing to use opioids postoperatively? If yes, provide drug name, frequency and amount over the past 24 hours.(4)How many days per week opioids are used at least once for operative pain?(5)Are you satisfied with your postoperative pain control (Likert scale 1–7)?

### Analysis

2.6

#### Sample size estimation (Table 1)

2.6.1

Existing literature suggests that single-shot ISNBs with general anesthetic could achieve mean postoperative recovery pain scores of 2 to 3 (on a 0–10 visual analog scale),^[35]^ and patients having general anesthetic with PAI block for shoulder surgery report pain scores of 5 to 6 (on a 0–10 NRS) at PACU.^5^,^36^,^37^ We considered a reduction in mean pain scores by 2 points to be clinically meaningful and important. We believe the ESP block has the potential to provide a good quality of analgesia, nearly similar to ISNB with less chance of phrenic nerve blockade. Based on these assumptions, we considered the following for our sample size analysis. For a 2-sided test, assuming a mean pain score of 5.5 (standard deviation of 2.5) in the control (PAI) group, a sample size of 25 per group will have 80% power to detect a statistically significant difference in mean pain scores of 2 or more using a Student *t* test, with an alpha set at 0.05. We expect minimal loss through attrition as the observations happen in hospital before discharge. However, considering the possibility of changes to surgical plan, we decided to set the sample size at 30 per group (which could give us 85% power). Sample size was estimated using (http://biostat.mc.vanderbilt.edu/wiki/Main/PowerSampleSize#PS:_Power_and_Sample_Size_Calculation), version 3.0.43.

**Table 1 T1:**
[figure not shown]
Sample size estimation table.

#### Statistical analysis

2.6.2

The trial will be reported as per the consolidated standards of reporting trials standards for reporting randomized trials.^[38]^ The study will be analyzed using an intention-to-treat (ITT) approach. For ITT, we will analyze patients within their randomized groups. We will use multiple imputation strategy to account for missing outcomes in ITT. Normally distributed continuous data will be reported as means and standard deviations; skewed continuous data will be reported as medians and quartiles (Q1 and Q3); and nominal data, categorical or binary data will be reported as counts and percentages. Comparison of normal continuous outcomes will be performed using Student *t* test for unpaired groups. Comparison of non-normal or skewed continuous outcomes will be performed using Mann–Whitney *U* test. Categorical outcomes will be compared using Pearson Chi-squared test. Each test will be 2-sided with a significance level of 0.05. Up-to-date versions of SAS (Cary, NC) and SPSS (Chicago, IL) will be used to conduct all analyses. Dichotomous outcomes will be reported as relative risk and relative risk reductions and continuous outcomes as difference in means with standard deviations. Precision will be reported using 95% confidence intervals. No subgroup tests will be conducted. Individual outcomes and their analyses are summarized in Table 2.

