#### Secondary outcomes and measurement

2.5.2

The following secondary outcomes will be collected during the in-hospital stay and follow-up of study patients:

(1)Total opioid consumption in hospital (until discharge): opioid use will be converted into morphine equivalent dosage for analysis.(2)Pain intensity: pain scores with movement in PACU; pain scores at rest; and movement at readiness to discharge. Since patients will be asked not to move their shoulders by the surgical team, pain scores with movement will be collected by asking the patient to sit up from lying down position. Pain scores will be collected using the 11-point NRS scale.^[26]^ We will record the postoperative time of peak pain scores.(3)Safety outcomes: incidence of moderate to severe PONV and incidence of moderate to severe itching will be collected using validated scales^28^,^29^; incidence of ipsilateral diaphragmatic paralysis will be diagnosed using bedside US examination with sniff test,^[30]^ 30 minutes after admission. This has been observed to be valid and clinically feasible^[31]^; and incidence of respiratory depression^[32]^ and LA toxicity^[33]^ will be diagnosed based on clinical symptoms and signs. All these outcomes will be noted postoperatively in PACU and until discharge, unless specified.(4)Sensory blockade on the side of the operated shoulder: Sensory assessment of shoulder area will be performed by a trained research assistant. Sensory dermatomes corresponding to shoulder and upper arm and their blockade to cold sensation will be noted. In total we will observe sensory blockade in 7 dermatomal areas (Supplemental Digital Content (Appendix 1)) and compare the extent of blockade between the 2 groups by their median and range.^[34]^
(5)Patient satisfaction with postoperative analgesia: This will be recorded at hospital discharge and 24 hours and at 1 month after surgery (by a telephone call) and measured using a 7-item Likert scale.

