## Discussion

3

This RCT examines ESP block versus PAI in patients undergoing shoulder arthroscopy and assesses differences in pain scores and opioid consumption, as well as in safety and other patient outcomes. It will allow physicians to make an evidence-based choice in recommending ESP block for shoulder arthroscopy, and will provide data regarding the safety profile of ESP block. The advantages of the study would be establishing efficacy of the ESP block for shoulder arthroscopy, which could include lower pain scores, less opioid consumption and better patient satisfaction in PACU, at discharge and at 1 month. This study will also help provide an estimate of the incidence of side effects and complications of the ESP block including PONV, pruritis, diaphragmatic paralysis, and LA systemic toxicity.

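### Relative risk as the stated effect measure for every binary outcome would often be undefined for rare safety events at 30 per arm; a risk difference would not (minor)

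*Protocol article*

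**What the plan says.** Section 2.6.2 (Statistical analysis) of the protocol article gives one rule for each type of outcome. For the comparison of groups: "Categorical outcomes will be compared using Pearson Chi-squared test". For the effect measure: "Dichotomous outcomes will be reported as relative risk and relative risk reductions", with precision shown by 95% confidence intervals whose method is not named. Binary data are also to be described by counts and percentages. The section refers to Table 2 for the analysis of each outcome; that table is not shown in the text available.

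The binary safety outcomes in section 2.5.2 are moderate to severe nausea and vomiting, moderate to severe itching, ipsilateral diaphragmatic paralysis, respiratory depression and local anesthetic toxicity. The last two "will be diagnosed based on clinical symptoms and signs". No expected rate is given for any of them. Section 2.6.1 fixes the size: "we decided to set the sample size at 30 per group (which could give us 85% power"). The Discussion says that the trial "will provide data regarding the safety profile of ESP block".

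**The concern.** A relative risk needs events in the comparator arm. With none there, it does not exist; with none in either arm, the Pearson statistic does not exist either. With none in the ESP arm only, the relative risk is 0 and the relative risk reduction is 100%, whatever the true effect. These are the tables one would expect for a rare complication in two arms of 30.

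At stake is how the safety results read. The Discussion presents safety information as one product of the trial. Where both arms are empty, the stated measure conveys nothing about how large a difference remains possible. Where one stray event falls in the PAI arm, it yields a striking reduction that rests on almost no data.

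**Working it through.** **Inputs.** 30 per arm (section 2.6.1), 1:1 allocation (section 2.3.1), two-sided 5% tests and 95% intervals (section 2.6.2). Event rates are not in the document. They are assumed here as 1%, 2%, 5%, 10% and 20%, equal in the two arms.

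**The plan's own figure.** Section 2.6.1 takes "assuming a mean pain score of 5.5 (standard deviation of 2.5) in the control (PAI) group" and states that "a sample size of 25 per group will have 80% power to detect" a "difference in mean pain scores of 2 or more". The normal approximation gives n = 2 × (1.96 + 0.8416)² × 2.5² / 2² = 24.5, so 25 per group. Exact power for the t test is 79.1% at 25 and 86.1% at 30 per group, close to the stated 80% and 85%. The size was chosen for mean pain scores and is sound for them; it was not chosen for the safety outcomes.

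**Empty arms.** Let q = (1 − p)^30 be the chance that one arm has no events.
- Comparator arm empty, relative risk undefined: q
- Both arms empty, neither relative risk nor Pearson test computable: q²
- ESP arm empty and PAI arm not, relative risk reduction of 100%: q(1 − q)
- At least one arm empty: 1 − (1 − q)²

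| Assumed rate p | q | q² | q(1 − q) | At least one empty |
|---|---|---|---|---|
| 1% | 74% | 55% | 19% | 93% |
| 2% | 55% | 30% | 25% | 79% |
| 5% | 21% | 5% | 17% | 38% |
| 10% | 4% | 0.2% | 4% | 8% |
| 20% | 0.1% | about 0% | 0.1% | 0.2% |

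Example at 2%: q = 0.98^30 = 0.545; q² = 0.298; q(1 − q) = 0.545 × 0.455 = 0.248.

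**What a risk difference gives.** For 0/30 the Wilson upper limit is z²/(n + z²) = 3.84/33.84 = 11.4%. The Newcombe interval for 0/30 against 0/30 is therefore −11.4 to +11.4 percentage points. For 2/30 against 0/30 it is +6.7 points (−5.7 to +21.3). The exact two-sided 95% upper limit for an incidence of 0/30 is 1 − 0.025^(1/30) = 11.6%.

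**The test.** The expected event count per arm is 30p, below 5 for any rate under 5/30 = 16.7%. Full enumeration at 30 per arm puts the true size of the nominal 5% Pearson test at 0.03% (rate 1%), 0.3% (2%), 2.8% (5%), 5.4% (10%) and 4.9% (20%). Error is not materially inflated. Single tables can still mislead. For 0 against 4 events the pooled rate is 4/60, z = 0.1333/√(0.0667 × 0.9333 × 2/30) = 2.07, and p = 0.038; Fisher's exact p is 0.112.

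**The case against.** The strongest reply has five parts.

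- *Rarity is assumed.* This stands. The document gives no rates, and the difficulty fades at about 10%. Nausea, vomiting and itching may well be common enough to escape it. A reader might also infer that the investigators expect diaphragmatic paralysis to be uncommon. Section 2.6.1 says only that phrenic block should be less likely than with the interscalene block, which is a comparison and not a rate.
- *One empty arm does not remove every interval.* This stands. Only the simple log-scale interval fails. A score interval for the relative risk exists: 0 to 0.90 for 0/30 against 4/30, and 0 to 1.84 for 0/30 against 2/30. So the 93%, 79% and 38% for at least one empty arm should not be read as the chance that no result can be reported.
- *The raw data will be visible.* This stands. Counts and percentages are promised, so 0/30 against 0/30 would be seen. They do not by themselves give a comparison between groups with an interval.
- *The Pearson test is acceptable.* Largely right. A reader might infer an inflated false-positive rate from the small expected counts, but the enumeration shows at most about 5.4% at the rates checked. Fisher's test is more conservative still, and the choice between them is debated.
- *Details belong in Table 2 or a fuller plan.* Partly right. Table 2 may name other analyses, and a missing fallback rule alone would not be a fault in a condensed article. But section 2.6.2 states the relative measure for binary outcomes without qualification, and that stated choice is the point here.

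**Conclusion.** The point holds as a minor one. For outcomes with true rates of about 2% or less, the stated measure is undefined in more than half of trials of this size (55% at 2%, 74% at 1%). At 5% it is undefined in about one in five (21%). A spurious 100% reduction in favor of ESP arises in 17% to 25% of trials at rates of 1% to 5% when there is no true difference. At 10% or more, at least one arm is empty in 8% of trials or fewer, and the matter is of little weight.

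These figures rest on equal rates in both arms, 30 analyzed per arm and rates that the document does not supply. The outcomes are secondary, and the primary comparison of pain scores is untouched. The documents do not support the stronger reading that the safety results would be unreportable, or that the chi-squared test would be seriously invalid.

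**What to change.** In section 2.6.2, and in Table 2 if it differs, state for the binary safety outcomes:

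- Report counts and the risk difference with a Newcombe or Miettinen–Nurminen 95% interval.
- When no event occurs in the ESP arm, give the exact upper limit for its incidence (11.6% for 0/30).
- Report the relative risk, with a score interval, and the relative risk reduction only where both arms have events.
- Where an expected count is below 5, an exact or mid-p test may replace Pearson chi-squared. This part is optional; its purpose is to avoid overreading single sparse tables.

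The cost is a few lines of analysis wording, with no change to data collection or sample size. If Fisher's test is chosen it will be conservative; the mid-p version lessens that.

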**Table 2 T2:**
[figure not shown]
List of outcomes, measurement, and analysis.

### Project coordination and reporting

2.7

This trial will be coordinated from the research office at the McMaster Department of Anesthesia and conducted at St. Joseph's Healthcare Hamilton.

### Data management and quality control

2.8

Data collection will be done using paper forms and transferred to REDCap for secure storage and analysis. REDCap is a secure web application developed to optimize data collection and management for research studies. All patients will receive a study ID to keep their information anonymous. Data will be collected by research assistants and nurses in the PACU and DSU and after discharge. The research coordinator will monitor the REDCap and ensure that the data are appropriately entered, verified, and kept secure. Only the research assistants involved with the study, the coordinator, and the study statistician will have access to the patient data. The REDCap database will be stored on a server in a data center located within the McMaster University campus. The data collection forms will also be kept in the locked cabinet.

### Risk assessment and protocol adherence

2.9

This trial does not entail any higher risk than the standard of care to patients. Medications of known benefit are used in clinically acceptable doses. Patients are managed using standard preoperative, OR, PACU, and DSU protocols. The ESP block will be performed by anesthesiologists competent with the block.

### Patient and public involvement

2.10

Patients and public were not directly involved in the development of the study protocol. We will disseminate the results to the study participants through the journal publication as well as from our research website.

## Discussion

3

This RCT examines ESP block versus PAI in patients undergoing shoulder arthroscopy and assesses differences in pain scores and opioid consumption, as well as in safety and other patient outcomes. It will allow physicians to make an evidence-based choice in recommending ESP block for shoulder arthroscopy, and will provide data regarding the safety profile of ESP block. The advantages of the study would be establishing efficacy of the ESP block for shoulder arthroscopy, which could include lower pain scores, less opioid consumption and better patient satisfaction in PACU, at discharge and at 1 month. This study will also help provide an estimate of the incidence of side effects and complications of the ESP block including PONV, pruritis, diaphragmatic paralysis, and LA systemic toxicity.

### Potential pitfalls

3.1

The primary outcome is the subjective pain scores using NRS scales. These are validated scales, although they do possess some inherent limitations. For equianalgesic dose ratio and conversion to morphine equivalent units we have used the Faculty of Pain Medicine of the Australian and New Zealand College of Anaesthetists document, although other ratios and scales have been reported in the literature (http://fpm.anzca.edu.au/documents/opioid-dose-equivalence.pdf).

### Ethics and dissemination

3.2

The study has been approved by the Hamilton Integrated Research Ethics Board. We plan to report and publish our study findings in a high-impact medical journal, with online access. We also plan to present it at selected conferences and scientific meetings.
